### Statistical Protocol

All children will be measured regarding the variables of interest (Table 1) before the implementation of PAAC starts at each intervention school as well as in the control schools (baseline). At the end of the first school year with PAAC in intervention schools, all children will be measured/tested again (1st follow-up). The same measurements/tests will be performed after the 2nd and 3rd year of implementation in all schools.

All data collected will be explored with regard to their distribution and potential outliers before being further analyzed. Main focus of the analyses will be the evaluation of changes in parameters of interest (physical fitness, anthropometry, quality of life, cognition etc.) from baseline to follow-up(s), depending on the intervention. Thus, comparing if the magnitude of change differs between children from intervention schools compared to children of the control schools. Depending on the number of variables and time-points to be compared in one analysis, dependent *t*-tests, repeated measures ANOVA and/or ANCOVA will be performed. Accordingly, a higher increase of, e.g., physical fitness in children of the intervention schools compared to children of a control school is expected.

In case of violations against the assumptions of parametric tests, either data transformations or application of non-parametric tests will be performed.

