The current project builds upon the HOPP project, and by active collaboration between the consortium members, excellent teaching will be promoted and skills developed to encourage PA in the lectures (46). The intervention will be performed by teachers of the participating schools for at least 3 years. Involved researchers will support development and adaptation of methodology, and will perform measurements to assess health and academic effects. Although the design does not allow for randomized assignment of participants, the natural environment in the sense of a field study with familiar teachers performing a new pedagogy (PAAC) as well as the large number of participants will—together with a case-control methodology—provide a stronger knowledge platform than smaller-scale RCT studies.

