### Population and Sample Size

Schools will be invited to participate either as intervention or control school. In the attempt to be most inclusive, all children of grades 2 and 3 of the participating schools are allowed to take part. In intervention schools, all children will be taught with PAAC, though only children whose parents/legal representatives gave written informed consent will be included in the measurements of physical fitness, health parameters, cognitive/mental and social abilities. Children of both sexes, different socio-economic backgrounds and cultural contexts, and from urban as well rural areas will be enrolled. No child will a priori be excluded, neither from physically active learning nor from the measurements performed. However, any pre-existing disability or illness will be recorded and considered when validating the results for the children. Furthermore, each child may deny participation at any time in the course of the study or for a certain measurement.

In each country, aged-matched children of a different school will be included as the control group. Healthy children of both sexes, aged 7–9 years (in grade 2–3), will be tested at the same time intervals as children from the intervention schools. Children in the control group will not receive active learning throughout the duration of the project, but will be taught according to the usual didactics.

Assuming that the prevalence of NCDs varies across schools, following a normal distribution with a mean value of 3% and a SD of 2%, a prevalence rate of about 5% would be expected. The power calculation for the intervention study is based on the change in a quantitative outcome variable from baseline to follow-up. Annually analyses between intervention and control schools in numerous variables, the sample size for a parallel group design is calculated using *n* = 2 · (σ / Δ) 2 · k, where n represents the number of participants in each group, σ (sigma) the expected standard deviation of the observations (which is assumed to be equal for all groups), Δ (delta) gives the relevant difference between observations, and k is the constant in this study, chosen based on the common values by a double-sided *t*-test set at 5% and with test strength 80% (this corresponds to a *k* of 7.9). Based on these calculations we have determined the sample size to be adequate for all variables for all ages, also when divided by sex (Table 1).

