**Table 1 T1:** Based on the various tests, the following sample sizes for each group (intervention and control schools) were calculated as adequate for analyses, with a power of 80% and alpha of 5%.

	**Variables**	**Methods**	**Number of children in each group/total**
Anthropometry	Weight, height, IsoBMI, fat-, fat-free and muscle-mass, WHtR	Measuring tape, body composition analyzer	34^*^/68 and 64^**^/128
Physical activity level	MVPA 60 min/day, VPA (min/day) and inactivity (min/day)	24-h activity monitor (Actigraph) for 1 week	126^***^/252
General physical capacity (fitness)	Strength test (kg) and Andersen Running Test	Jamar Handgrip	73^*^/146
Blood values	HDL and total cholesterol, Glycated hemoglobin (HbA1c), hemoglobin, hematocrit, ferritin, iron, and red blood cell (RBC) count	Blood analysis	126^***^/252
Quality of Life and SDQ?	LQ_0−28_	ILC questionnaire, parental and child response	34^*^/68
Diet	Intake of fat, sugar, fruit/vegetables and confectionary in diet	Questionnaire	73^*^/146
Cognitive ability	Executive functions	Eriksen flanker test Stroop test	24^*^/48
Behavioral screening	Mapping of emotions, body image and friendship	BUS-Test	85^*^/170
Academic performance	Score in national test for English, Mathematics and native language	Local and national academic tests	34^*^/68

*Statistical program: Systat 13, Power analyses*.

* *one-sample t-test*,

** *two-sample t-test*,

*** *Z-score*.

In the present study we will recruit ~3,000 + pupils in three countries. As can be seen in Table 2, the number of pupils recruited are sufficient for analyzing the questions established in Table 1.

**Table 2 T2:** Estimated sample size for HAPHC.

	**Intervention schools**	**Control schools**	**Total**
Austria	558	198	756
Slovenia	936	225	1,161
Belgium	798	398	1,196
Total *n* of children	2,292	821	3,113

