### Selection of Partners

The involved partners in the project are selected on the ground of interest in the field, and the availability to be a participating school. The research collaborators will be selected as they have experienced either data collection and interpretation, development of learning toolkits, organization of workshops or implementation of PAAC in schools. Elementary schools in which the PAAC are to be implemented will be selected based on interest and earlier collaboration with the scientific groups in the respective countries.

Comparing the involved countries in it's current PA status is in itself important, however, establishing an pan-European and culturally transferable teaching toolkits for elementary school teachers and faculties for education with the goal of increasing every countries PA status, health improvement and learning results *via* involvement of these key stakeholders from municipalities, schools and regional administrators, would have in it an health improving capability of tremendous dimensions. These partners will help in establishing good habits for PA on a regular and continuous basis, simultaneously with improved academic performance, in early childhood may have a large impact on future health. Furthermore, an important aspect of including partners from different countries is also that each country has a different educational context, in terms of practices, beliefs toward PA and what constitutes overweight and obesity. For instance, Norway has in the last decade acquired a relatively large knowledge around how to inspire the population, especially children, in increasing the PA level for the benefit of health.

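### The comparison is stated by arm only although the country mix differs between arms, and the claim of a stronger basis than smaller randomised trials is not supported

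*Protocol article*

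**What the plan says.** **Allocation.** Under Population and Sample Size: "Schools will be invited to participate either as intervention or control school". Under Selection of Partners, the schools that are to implement PAAC "will be selected based on interest and earlier collaboration with the scientific groups in the respective countries". The same sample-size section provides local controls: "In each country, aged-matched children of a different school will be included as the control group".

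**Analysis.** The Statistical Protocol states the aim as "Thus, comparing if the magnitude of change differs between children from intervention schools compared to children of the control schools", using dependent t-tests, repeated measures ANOVA and/or ANCOVA. It names no country or school factor and no covariate.

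**Academic outcome.** Table 1 gives the variable as "Score in national test for English, Mathematics and native language" and the method as local and national tests. The abstract lists academic achievement among the primary outcomes.

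**Strength of the design.** Under Training Teachers in Implementing the PAAC Program, one sentence opens "Although the design does not allow for randomized assignment of participants". It goes on to say that the natural setting and the large number of participants, combined with a case-control methodology, will "provide a stronger knowledge platform than smaller-scale RCT studies". Possible Limitations mentions neither selection of schools nor confounding.

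**The concern.** There are two separate problems.

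First, the arms draw on the three countries in different proportions. A contrast of all intervention children with all control children therefore mixes the effect of PAAC with any difference between countries in how children change over the study years. The article itself says, under Selection of Partners, that educational context differs by country. For academic outcomes the instruments may differ as well, so raw scores have no stated common scale, and taking change from baseline does not create one.

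Second, the article credits the design with a strength that it lacks. Large numbers reduce random error. They do not reduce bias from choosing PAAC schools for their interest and earlier collaboration. With several thousand children, such a bias would be estimated precisely and could pass for an effect. Case-control is also the wrong label: children are grouped by exposure and followed forward, and Aims and Objectives calls the study longitudinal and controlled.

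**Working it through.** **Inputs (Table 2), intervention / control**
- Austria 558 / 198, Slovenia 936 / 225, Belgium 798 / 398.
- The article's totals reproduce: 558 + 936 + 798 = 2,292; 198 + 225 + 398 = 821; 2,292 + 821 = 3,113.

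**Country mix**

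| Country | Ratio | Share of intervention | Share of control | Difference |
|---|---|---|---|---|
| Austria | 2.82 | 24.3% | 24.1% | +0.002 |
| Slovenia | 4.16 | 40.8% | 27.4% | +0.134 |
| Belgium | 2.01 | 34.8% | 48.5% | −0.137 |

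**Bias of a crude pooled contrast.** With no PAAC effect, the expected difference between arms is the sum over countries of (intervention share − control share) × mean change in that country. If Slovenia differs from the other two by a gap g and those two are alike, this is 0.134 × g. If Slovenia and Belgium differ by g with Austria midway, it is 0.135 × g, which is practically the same.

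**False-positive rate.** The article gives no between-country gap in change, so g is an assumption, in units of the within-country SD of change. With independent children, SE = √(1/2,292 + 1/821) = 0.0407 SD. The two-sided 5% test rejects with probability Φ(−1.96 − b/SE) + 1 − Φ(1.96 − b/SE), where b is the bias.

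| Assumed g (SD) | Bias (SD) | b/SE | Rejection with no PAAC effect |
|---|---|---|---|
| 0.1 | 0.013 | 0.33 | 6% |
| 0.2 | 0.027 | 0.66 | 10% |
| 0.3 | 0.040 | 0.99 | 17% |
| 0.5 | 0.067 | 1.65 | 38% |

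**With a clustered standard error.** Take 12 equal schools (abstract) of 3,113/12 ≈ 259 children and an assumed intraclass correlation of 0.01 to 0.05. The design effect, 1 + (259.4 − 1) × ICC, is 3.58 to 13.92, and the SE is 0.077 to 0.152 SD. At g = 0.5 the rejection rate falls to about 14% to 7%. The bias itself stays at 0.067 SD.

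**Cost of a within-country estimate.** SE = 1/√Σ[1/(1/n_I + 1/n_C)] = 1/√(146.1 + 181.4 + 265.6) = 0.0411 SD, against 0.0407. The difference detectable with 80% power (2.80 × SE, independent children) goes from 0.114 to 0.115 SD.

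**What a country term does not cure.** Suppose PAAC schools would have changed more than their own country's controls anyway, by an assumed 0.05, 0.10 or 0.20 SD. The within-country test with SE 0.0411 still rejects in about 23%, 68% or over 99% of cases with no PAAC effect.

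**The case against.** A reader might infer that the trial will pool the countries and read their differences as a PAAC effect. The article does not say so. The Statistical Protocol names a contrast and a family of methods that includes ANCOVA; it neither specifies a crude pooled test nor rules out country. Controls are recruited in every country, and Table 2 is set out by country. A condensed article may leave covariates to an analysis plan that is not shown. This stands, and it makes the bias conditional on how the contrast is run. What remains is that the only comparison on the page is by arm and does not use the in-country controls.

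The size is also open to challenge. Stable differences in level between countries cancel in change scores on a common scale, Austria's share is balanced, and only about 13% of a gap in change leaks through. At gaps of 0.1 to 0.2 SD the harm is small, and the higher rates treat children as independent. All of this stands. It does not help the academic outcome, for which no common scale is stated.

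Finally, a reader might take the design statement as saying that sample size alone outdoes randomisation. It is narrower: it compares with smaller-scale randomised trials, cites the field setting and familiar teachers as well as numbers, and concedes that assignment is not randomised. A field setting may help applicability, but it does not remove selection of schools, so the claim is still unsupported.

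**Conclusion.** The point holds in two parts.

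**Country.** The comparison is stated by arm only, in a design where the country mix differs clearly between arms. A crude pooled analysis would carry 0.013 to 0.07 SD of bias for assumed gaps in change of 0.1 to 0.5 SD. Type I error would be about 6% to 38% with independent children, and lower with a clustered standard error. These figures rest on assumed gaps, on the planned numbers in Table 2, and on the contrast actually being run without country, which the article leaves open. For academic scores the need to handle country does not depend on those gaps, because local and national tests cannot be taken as one scale.

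**Design claim.** The statement of superiority over smaller-scale randomised trials and the case-control label are wrong as printed, and no separate analysis plan would correct them. School self-selection remains whatever the number of children, and adjustment for country leaves it in place.

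**What to change.** - **Model.** Estimate the effect within country and combine: include country and country-by-visit terms, adjusted for baseline value, age and sex. In a repeated-measures model the country-by-visit term is the one that absorbs differences in change; a country main effect alone captures level.
- **Academic scores.** Standardise within country and grade at each wave before pooling.
- **Wording.** Withdraw the comparison with smaller-scale randomised trials and the case-control label. Describe the study as a non-randomised controlled study.
- **Limitations.** Add self-selection of schools, and say that neither sample size nor a country term removes it.

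**Cost.** Country is known for every child. The child-level loss of precision is negligible (0.0407 to 0.0411 SD). At school level the country terms use two degrees of freedom among about 12 schools: 12 − 2 = 10 becomes 8. That is affordable but not free, more so if only the nine schools confirmed under Possible Limitations take part (9 − 2 = 7 becomes 5). The rest is wording.

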**Methods:**

In three European countries (Austria, Slovenia, and Belgium), 12 primary schools in total will be recruited to act as either intervention or control school in a large intervention study, which applies the PAAC pedagogy during lectures. It is estimated that, at least 3,000+ children across the three countries will be recruited in this study. All teachers of intervention schools will receive training and materials/teaching equipment that will allow them to integrate a daily PA unit of 45 min over 3 years across the curriculum. In response to the daily PA intervention, the following primary outcomes will be assessed: changes in health related physiological factors, academic achievement, psycho-social aspects and wellbeing.

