### Ethical Considerations

After detailed information on the project aims and measurements performed on children, which will be provided within teacher-parents evenings by researchers and local teachers, written informed consent forms signed by the parents or legal representatives will be collected. Children without permission to participate will only take part in the pedagogy, which will be performed in all classes of each intervention school. Furthermore, children will be given a detailed explanation and demonstration of the measurements before their consent forms will be collected, and will be given the chance to deny a certain measure or test at any time in the course of the study. All data will be anonymized and measures will be conducted according to the principles stated in the Declaration of Helsinki (2013). Data on physical characteristics such as height, weight, strength etc. will not be verbally communicated in the presence of other children.

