## Possible Limitations

Although the HAPHC project will provide novel information, some limitations have to be considered:

At date, Austria has confirmed the partnership of three schools, Slovenia and Belgium also of three schools. Unexpected circumstances will be avoided by regular communication and strategy planning, including changing project partner schools. Parents/legal representatives will be informed preliminary about the aims, goals and activities.Another limitation may be that outreach activities may not be completed on time. The planned interaction with EU initiatives and involving partners from other regions will strongly support outreach.A high risk is that not all the key stakeholders may be engaged by the project in time to carry out appropriate dissemination. It will be ensured that all the stakeholders are engaged and contacted on time. Roles of each partner who should be responsible for which stakeholder have to be identified, although with flexibility.A risk is also that a partner drops out, however, all partners have a long tradition of collaboration in different settings, so it is considered to be a low risk. Each partner contributes by being present with his or her specialized competencies and tasks. In case a partner leaves the project, the other partners will cover the lost competences and a substitution will be considered.

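### PAAC is assigned to whole schools, but the named tests compare change between children with no provision for school, so standard errors are too small and 5% tests reject too often

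*Protocol article*

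**What the plan says.** Assignment is by school. In the abstract's Methods, "12 primary schools in total will be recruited to act as either intervention or control school"; under Population and Sample Size, "Schools will be invited to participate either as intervention or control school". Ethical Considerations describes the pedagogy as one "which will be performed in all classes of each intervention school", so arm never varies within a school. Possible Limitations reports fewer schools so far: "Austria has confirmed the partnership of three schools, Slovenia and Belgium also of three schools". For controls, in each country "aged-matched children of a different school will be included as the control group", which reads as one control school per country, but the split of schools by arm is not stated.

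The sample size is per child. The formula is n = 2(σ/Δ)²k, "where n represents the number of participants in each group", with k taken for a "double-sided *t*-test set at 5% and with test strength 80% (this corresponds to a *k* of 7.9". It has no design effect and no ICC.

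The analysis is per child too. The Statistical Protocol compares the size of change between children of the two kinds of school and chooses, "Depending on the number of variables and time-points to be compared in one analysis", among dependent t-tests, repeated measures ANOVA and ANCOVA. Its only fallback is transformation or non-parametric tests when parametric assumptions fail.

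**The concern.** Children in one school share teachers, the way PAAC is delivered, and testing conditions. Their changes over a year are therefore likely to be correlated. The repeated-measures part of the named tests deals with correlation between visits of one child, not between children of one school. Standard rank tests, the stated fallback, also assume independent children.

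The true amount of independent information on the arm effect lies closer to the 9 to 12 schools than to the 3,113 children. If the tests are run as named, a difference in trend between a few schools can come out as a significant PAAC effect. The article plans annual comparisons on many variables and intends the results to support transfer across Europe, so an inflated error rate matters here.

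**Working it through.** **1. The plan's own figures.** k = (1.960 + 0.842)² = 7.85, which rounds to the stated 7.9. The article gives no σ or Δ, so Table 1 can be checked only under an assumption. At an assumed standardised difference of 0.5, a two-sample t-test needs 63.8, so 64 per group, and a one-sample t-test needs 33.4, so 34. Both numbers appear in Table 1. They are reached with no allowance for clustering.

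**2. Inputs.** From Table 2: 2,292 intervention and 821 control children. Assumed, because not stated: schools split 9+3, 6+3 or 6+6 (intervention + control), equal school sizes within arm, all children measured, and the ICC for change.

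**3. Formulas** (in SD units of change, m = children per school, subscript 1 = intervention, 0 = control):
- design effect per arm: DE = 1 + (m − 1) × ICC
- true variance: DE₁/2292 + DE₀/821
- child-level variance: 1/2292 + 1/821 = 0.001654
- R = √(true variance / child-level variance)
- real two-sided error = 2 × [1 − Φ(1.96 / R)]

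**4. Worked case, 9+3 schools, ICC 0.01.** m₁ = 2292/9 = 254.7 and m₀ = 821/3 = 273.7. DE₁ = 3.54 and DE₀ = 3.73. True variance = 3.54/2292 + 3.73/821 = 0.00608. R = √(0.00608/0.001654) = 1.92. Error = 2 × [1 − Φ(1.96/1.92)] = 31%.

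**5. Range.**

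| Assumed ICC | 9+3 | 6+3 | 6+6 |
|---|---|---|---|
| 0.001 | 8% | 9% | 7% |
| 0.005 | 20% | 22% | 17% |
| 0.01 | 31% | 33% | 26% |
| 0.02 | 44% | 46% | 38% |
| 0.05 | 61% | 63% | 56% |

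A simulation with country-specific school sizes gave 31% (12 schools) and 34% (9 schools) at ICC 0.01, and 62% and 63% at 0.05. A t-test on school means stayed near 5% throughout.

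**6. A proxy from the article.** Population and Sample Size assumes that NCD prevalence varies across schools with mean 3% and SD 2%. Read as between-school variance, this gives ICC = 0.02² / (0.03 × 0.97) = 0.0137. With 9+3 schools, R = 2.16 and the error is 36%; with 6+3 it is 39% and with 6+6 it is 31%. If the 2% is instead an observed spread over schools of about 260 children (3,113/12), binomial variation of 0.03 × 0.97/260 = 0.000112 must come off, and the ICC is (0.0004 − 0.000112)/0.0291 = 0.010.

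**7. Fewer children measured.** If half are measured (1,146 and 410.5) in 9+3 schools at ICC 0.0137, DE is 2.74 and 2.87, R = 1.68, and the error is 24% instead of 36%. At ICC 0.001 it is 7%.

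**8. Detectable difference at 80% power.** With independent children: √(7.85 × 0.001654) = 0.11 SD. At ICC 0.0137 with t quantiles on school-level degrees of freedom: 0.27 SD for 9+3 (10 df) and 0.30 SD for 6+3 (7 df).

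**9. Which random effects are needed.** Write a measurement as arm and visit effects + school effect + child effect + error. In the change from baseline, a school effect that is constant over visits subtracts out. A model with only school and child intercepts therefore leaves school-to-school variation in change out of the arm-by-visit standard error. In a simulation with no effect (9+3 schools, 20 children each, ICC of change 0.08, 150 runs), that model had a mean standard error of 0.148 against a true SD of 0.221, and it rejected 19%. The child-level formula gives 22% for the same setting (DE = 1 + 19 × 0.08 = 2.52). School means rejected about 5%.

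**The case against.** Several points on the other side stand.

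- A reader might infer that the protocol's own figures fix the ICC at 0.014 and the true error at 36%. The documents do not support this. The 3% and 2% describe a binary prevalence at one time point, NCD prevalence is not a Table 1 variable, and the power statement rests on change in a quantitative outcome. The 36% also depends on an assumed school split and on every child being measured, although measurement needs consent and a child may decline any test.
- A reader might infer that any ordinary difference between schools would be reported as a PAAC effect. The comparison is of change from baseline, so stable differences in level, such as those tied to neighbourhood, cancel. Only differing school trends do the damage.
- A reader might infer that the named models exclude school. The section lists no factors or covariates at all, so what can be said is that it makes no provision for school.
- The article condenses a fuller protocol, and an analysis plan may exist. That would excuse missing detail. Here, though, the tests are named, and a later plan would have to replace them, not elaborate them.

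None of this changes the direction of the error. No part of the article deals with correlation within schools.

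**Conclusion.** The point holds. Assignment is by whole school, the named tests work on children, and nothing provides for school, so the tests reject too often whenever school trends differ. The size depends on inputs that the article does not give. If all children are measured, inflation is modest at an ICC of 0.001 and substantial from about 0.005 upward, because schools average roughly 260 children. The ICC of 0.014 is a proxy and should be cited only as one. The article mentions no confidence intervals, but any interval built from these tests would inherit the same understated standard error. The statement that the recruited numbers are adequate for all variables rests on the same assumption of independence.

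**What to change.** In the Statistical Protocol, replace the child-level tests by one of these:

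- **School-level analysis.** Compare school mean changes between arms, allowing for country, with a t reference on school-level degrees of freedom.
- **Mixed model.** Fit arm, visit, arm-by-visit and country, with random effects for child, school and school-by-visit. For a single follow-up, use a child change-score or baseline-adjusted model with a school random effect. Use Kenward-Roger or Satterthwaite degrees of freedom.

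A school random intercept alone is not enough for the change contrast (step 9). School as a fixed covariate does not work either, because school is nested in arm.

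Report the ICC for each outcome. In Population and Sample Size and Table 1, restate the adequacy claim with a design effect, a stated ICC and the number of schools per arm.

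**Cost.** Analysis wording, some programming and a redone sample-size section; data collection does not change. Intervals become wider and degrees of freedom are few: 9 − 2 = 7 to 12 − 2 = 10, less two more if country is adjusted for at school level. The correction does not remove confounding from the non-random assignment of schools, which remains a separate limit.

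### Dependent t-tests are listed for a between-arm question that they cannot answer; used on their own, they could show maturation as a PAAC effect

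*Protocol article*

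**What the plan says.** The Statistical Protocol section of the protocol article gives the main analysis as "comparing if the magnitude of change differs between children from intervention schools compared to children of the control schools". Measurements are taken at baseline and after years 1, 2 and 3. The next sentence gives the methods: "dependent *t*-tests, repeated measures ANOVA and/or ANCOVA will be performed". The method is chosen as follows: "Depending on the number of variables and time-points to be compared in one analysis". The number of groups is not part of that rule, and the dependent t-test is the only t-test in the list.

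The Population and Sample Size section describes a two-group calculation ("the sample size for a parallel group design is calculated using" a formula with the factor 2 for two arms). Yet the footnotes to Table 1 mark most of the resulting sizes as "one-sample t-test". Table 2 expects 2,292 children in intervention schools and 821 in control schools. The article states that allocation is not randomised.

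**The concern.** The question compares two arms, whereas a dependent t-test looks at one. It tests whether the mean of follow-up minus baseline is zero in a single group, and no term in it refers to the other group.

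This matters because children aged 7–9 grow, become stronger and learn over one to three years however they are taught. A within-arm test can therefore be significant without any PAAC effect. In a study without randomisation, the concurrent control schools are the main means of separating PAAC from ordinary development, and a within-arm test does not use them.

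A second risk arises if the two arms are tested separately and the p-values compared. The larger arm reaches significance more easily for the same true change, and here the larger arm is the intervention arm.

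**Working it through.** **1. Can the dependent t-test be read as a between-arm test?** Only if children were paired across arms. The article says that controls are age-matched and come from a different school; it describes no individual pairs. With 2,292 and 821 children, one-to-one pairing would leave 2,292 − 821 = 1,471 intervention children unpaired. The natural reading is baseline against follow-up within an arm.

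**2. The plan's own constant.** For two-sided 5% and 80% power, k = (1.960 + 0.842)² = 7.85. The article states 7.9, so the constant reproduces.

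**3. Does the one-sample logic appear elsewhere?** Table 1 gives ten sizes per group. Seven are marked one-sample (34, 73, 34, 73, 24, 85, 34), one two-sample (64) and two Z-score (126, 126). Table 1 states no effect sizes, so they are back-solved here as an assumption:

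| Assumed standardised effect | One-sample t, n | Two-sample t, n per group |
|---|---|---|
| 0.5 | 34 | 64 |
| 1/3 | 73 | 143 |
| 0.6 | 24 | 45 |

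The 34, 73 and 24 of Table 1 are reproduced as one-sample sizes, and the 64 as a two-sample size at the same effect as the 34. The within-arm view is thus present in the sizing as well as in the list of tests.

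**4. Behaviour of within-arm tests with no PAAC effect.**

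Inputs: n = 2,292 and 821 (Table 2); two-sided 5%; the same true mean change d, in SDs of change, in both arms; children independent. The article gives no value for d, so a range is shown.

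Chance that one arm is significant: P(n) = Φ(d√n − 1.96) + Φ(−d√n − 1.96).

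Chance that only the intervention arm is significant: P(2,292) × [1 − P(821)].

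Example at d = 0.08:
- Intervention: 0.08 × √2,292 = 3.83, and Φ(3.83 − 1.96) = 0.969.
- Control: 0.08 × √821 = 2.29, and Φ(2.29 − 1.96) = 0.630.
- Intervention only: 0.969 × 0.370 = 0.36.

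| d (assumed) | Intervention significant | Control significant | Intervention only |
|---|---|---|---|
| 0 | 5% | 5% | 5% |
| 0.02 | 16% | 9% | 15% |
| 0.05 | 67% | 30% | 47% |
| 0.08 | 97% | 63% | 36% |
| 0.10 | 99.8% | 82% | 18% |
| 0.15 | 100% | 99% | 1% |
| 0.5 | 100% | 100% | 0% |

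The last column peaks at 49% near d = 0.058. With equal arms of 1,556 it would not exceed 25%. The reverse pattern, control only, is 2% at d = 0.08.

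**5. The between-arm test under the same conditions.** In 4,000 simulated trials per setting, a two-sample t-test on change scores rejected in 5.0% (d=0), 5.8% (d=0.08), 5.4% (d=0.10) and 5.2% (d=0.5). The simulation standard error is √(0.05 × 0.95 / 4,000) = 0.3 percentage points. The rate stays near 5% whatever the common change.

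**The case against.** The strongest defence is that the section states the between-arm question outright. Its list includes repeated measures ANOVA, which can carry a group-by-time term, and ANCOVA, which is a standard method for baseline plus one follow-up. The section then describes the expected result as a larger increase in intervention than in control schools. Nothing says that a PAAC effect will be claimed from separate within-arm tests. This stands: the harm is possible under the text but not planned by it, and two time-points do not force the dependent t-test.

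It does not remove the point. The rule for choosing a test does not mention groups, the dependent t-test is one of the permitted choices, and nothing confines it to description.

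A reader might infer two stronger things:
- **That growth and arm imbalance act together.** They do not. Once the common change is 0.15 SD or more, both arms are almost always significant and the intervention-only pattern disappears. Imbalance misleads for small common changes, roughly 0.02 to below 0.15 SD. For larger ones, the problem is the intervention arm's result read alone.
- **That repeated measures ANOVA will drop every child with a missed visit.** The article lets a child refuse a measurement but does not say how missing values are handled. That may be settled in the full protocol or analysis plan, so it is no part of this point.

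**Conclusion.** The point holds in a limited form. The article lists, without restriction, a test that cannot answer its own stated question, and its selection rule allows that test for the simplest comparison, one variable at baseline and one follow-up. Such an analysis could be significant from maturation alone.

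If within-arm results were compared across arms, a false intervention-only pattern would have a probability between 5% (d=0) and a peak of 49% (d near 0.06), falling to 1% at d=0.15. These figures assume equal true change in both arms, independent children, and the estimated numbers of Table 2 fully measured. School clustering is ignored. No single value of d can be taken as the expected one.

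The documents do not support the reading that false PAAC effects would follow from the plan as a whole, because two of the three listed methods can test the between-arm contrast. The point should be corrected, and the correction is small.

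**What to change.** In the Statistical Protocol section, remove dependent t-tests as a test of the PAAC effect and keep them, if wanted, as descriptive summaries of change within each arm. Add one sentence stating that inference on PAAC rests on the between-arm contrast in change: either the group-by-time term of the repeated measures model or ANCOVA of the follow-up value adjusted for baseline. Both methods are already listed.

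The cost is a change of wording. It needs no new data, visits or software.
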